## Abstract

**Background:**

Hospital-Based Violence Intervention Programs (HVIPs), based in Emergency Departments (EDs), have been proposed as a public health response to violence. These programs address the underlying reasons why patients are exposed to violence. In addressing any underlying modifiable risks and vulnerabilities HVIPs can reduce patients’ exposure to violence and therefore subsequent unplanned attendance into ED.

**Objective:**

The objectives of this study are to (1) assess whether patient involvement with a HVIP reduces the likelihood of unscheduled ED reattendance, (2) determine whether the presence of the HVIP improves ascertainment of violence in ED attendances, and (3) derive the costs of the HVIP and compare those to the benefits of the intervention and understand whether the HVIP represents value for money from a health service perspective. If an effect is observed, then models will estimate the health impacts, costs and potential savings over a longer time (eg, 10 years) period and for a national roll-out.

**Methods:**

ED patients are eligible for inclusion in the evaluation if they are normally resident in Wales, United Kingdom, aged 11 years and older. A controlled longitudinal natural experiment will be undertaken. The primary outcome is derived from the Emergency Department Dataset, routinely collected for all EDs in Wales, and is subsequent unplanned ED attendance. Case patients will be matched to control patients attending EDs without an HVIP. Analysis will derive the hazard rate for subsequent unplanned ED attendances using recurrent event analysis. The total monthly count of patients identified as attending because of violence in intervention EDs will be compared to the total count of Welsh control EDs in an interrupted time-series analysis to determine whether HVIPS increase violence ascertainment. To determine whether referral, versus no referral, to the HVIP represents value for money, we will undertake a cost-effectiveness analysis from the perspective of the National Health Service. The approval to access and analyze data housed in the Secure Anonymized Information Linkage (SAIL) databank, an ISO (International Organization for Standardization) 27001 certiﬁed and UK Statistics Authority accredited secure data environment, was granted by the SAIL independent Information Governance Review Panel (Ref: 1421). Findings will be presented at local, national, and international conferences and disseminated by peer-reviewed publication.

**Results:**

Design inputs arising from public patient involvement and engagement (PPIE) are reported. As a protocol, no further results are available.

**Conclusions:**

Novel methods are developed to provide the first robust evaluation of Emergency Department Violence Intervention Programs (EDVIPs).

**Trial Registration:**

ISRCTN Registry ISRCTN68945844; https://www.isrctn.com/ISRCTN68945844?q=68945844&filters=&sort=&offset=1&totalResults=1&page=1&pageSize=10

**International Registered Report Identifier (IRRID):**

PRR1-10.2196/86247

## Introduction

### Background

Those who experience serious injury due to violence are likely to attend an Emergency Department (ED). EDs are therefore ideal locations for Hospital-Based Violence Intervention Programs (HVIPs) [1-3]. HVIPs have recently emerged as a public health response to violent victimization [3,4], but despite interest in HVIPs, there has been no rigorous evaluation of this public health approach to violence in the United Kingdom. Moreover, little is known about the effectiveness of patient discharge planning and referral from ED into organizations able to support children involved in violence [5] and patients exposed to domestic violence [6,7], and there is a paucity of studies considering referrals for young men involved in violence, the most dominant population in respect of Assault-Related Attendance (ARA) [8]. There are even fewer studies of the effective support available to victims of sexual violence attending ED [9]. Despite uncertainty over effectiveness in a UK context, HVIPs have begun to be implemented. For example, the Scottish Violence Reduction Unit (VRU) has placed navigators in EDs, typically youth workers who connect with patients aged 25 years and younger [10].

EDs work with patients attending for many reasons, including those presenting with violence-related injuries. EDs also engage in broader violence reduction initiatives, clinical staff typically receive training in adult and pediatric safeguarding, and many EDs have provisions to identify and refer children and victims of domestic and sexual violence. However, methods of ascertainment and referral vary considerably, and formal relationships with the police and other partners can often lack continuity, with multiagency approaches not capturing the entirety of patients’ journeys. A public health approach involving the ED would be beneficial in improving overall population health outcomes. It is particularly timely; in 2019 there were 175,764 ARAs at EDs in England and Wales [11] and, despite the pandemic, 119,111 ARAs in 2020 [12]. Knife crime, and therefore serious trauma, has risen by 71% from 2014 to 2018 [13]. Up to 75% of ARAs are unknown to the police [14-16]; therefore, EDs hold exclusive data on assault characteristics, patient vulnerabilities, and modifiable risks and are therefore well situated to play a significant role in the identification of violence, to investigate the circumstances of violence, and to challenge any underlying vulnerabilities or modifiable risks exposing patients to violence, whether that is through direct support, referral, or discharge planning.

The need for HVIPs is aligned to broader UK Government initiatives, which aim to promote a whole system multiagency (WSMA) [17] approach to violence. The 1998 Crime and Disorder Act requires the police, local government, and the National Health Service (NHS) to collaborate on joint crime reduction strategies, and this includes data sharing to inform targeted responses. Violence reduction is further prioritized by the UK Government in its serious violence strategy [18], and the UK Government has allocated funds for the formation of VRUs in England and a violence prevention unit (VPU) in Wales, across 18 Police and Crime Commissioner jurisdictions, with the explicit purpose of promoting the WSMA approach [19]. These initiatives are further aligned with a move toward active population health management, digitally enabled whole-person care, and evidence-based treatment pathways outlined in the NHS future plan [20]. Integrated care systems in NHS England will be expected to specify violence prevention and reduction standards, which are incorporated into the 2021/22 NHS Standard Contract, and there are expectations that hubs will form Violence Prevention Teams (VPTs) similar to the police VRUs and VPU. Furthermore, a public sector duty on partnerships encouraging the prioritization of reducing serious violence has received royal assent as a part of the police, crime, sentencing, and courts bill. This legislation includes a serious violence duty, placing a statutory obligation on organizations to collaborate, communicate, and act.

The overarching aim of the work proposed here is a robust effectiveness and cost-effectiveness evaluation of ED-based VPTs. VPTs represent a formal collaboration between police and health care and embody the WSMA approach. To our knowledge, this is the first formal evaluation of a nurse-led, ED-based HVIP in the United Kingdom and will address significant gaps in current understanding of their effectiveness and thereby facilitate future aspirations for evidence-based referral pathways and discharge planning [20,21]. VPTs main function is to identify and support patients attending ED with assault-related injury. To facilitate this, they engage in broader pedagogical roles, increasing awareness of these patients’ needs, modifiable risks, and opportunities to identify and refer across the ED clinical environment.

### Theoretical Framework

The theoretical motivation for a WSMA approach to HVIPs is that there are many modifiable risks and vulnerabilities that, in combination, determine an individual’s exposure to violence and subsequently an ARA in an ED. Epidemiologically, these can be usefully described by shared circumstances that in turn signpost opportunities to modify risk or support patients’ vulnerability, but responsibility can fall across organizations, including local government, health care, and criminal justice. Risks include the consumption of alcohol and other psychoactive substances [22-25]; criminal and/or sexual exploitation and homelessness [3,26]. Violence tends to be more prevalent in younger, socially disadvantaged groups [27-33], with male, socioeconomically deprived individuals being more likely to endure violence and experience assault-related injury. These characteristics further extend to personality features [34], including mental health status and learning disability, and neurodevelopmental disorders [35]. This complex interplay of factors that promote exposure to violence, and hence lead to an ARA, highlight the need for a WSMA approach. For example, an environment might become synonymous with violence through a process of homophile [36], whereby individuals with shared pursuits who are at risk of violence gather, for example, street drinkers and late-night drinking environments. Mitigation might include challenging reasons for frequenting such an environment, including alcohol and substance misuse counseling. Some environments might involve those who use violence to advance their interests, such as acquisitive crime, sexual assault, or sexual exploitation, in which case criminal justice or safeguarding processes to deter violence might be involved, along with support to victims. Chaotic or otherwise disadvantaged households in which domestic violence or harm to children arises might best be approached from a multiagency process such as the Multi-Agency Risk Assessment Committee (MARAC) and formal investigation (Section 47, Children Act 1989). EDs are primary agencies receiving those who have sustained a serious injury, including those who are motivated to bypass other agencies or whose assailant is motivated to ensure their victim avoids scrutiny.

Treatment for an ARA in ED aims to address symptoms (eg, injury) that may not necessarily characterize the underlying reasons for violence (eg, alcohol dependency), and staff do not always have the resources available to address such modifiable risks and vulnerabilities. However, without addressing them, the risk of repeat unscheduled ED attendance remains, including violence recidivism. For these reasons, services like VPTs that work within a WSMA approach to better understand reasons for ARA are required. Moreover, for those who are most vulnerable, ED may be the only realistic opportunity for patients to enter a system of care. As such, an ARA is often a sentinel event.

### Aims and Objectives

The overarching aim of the Emergency Department Violence Intervention Program Evaluation (EDVIPE) is to determine whether VPTs are effective and cost-effective from the perspective of the NHS.

Objective 1: to assess whether patient involvement with a VPT reduces the likelihood of unscheduled ED reattendance. We consider case and control patients’ ED unscheduled reattendance for a minimum of 12 months following the initial ARA.Objective 2: to determine whether the presence of the VPT improves ascertainment of ARAs in ED attendances. We will consider the change in identified ED ARAs across intervention implementation in case and control EDs in Wales.Objective 3: to derive the costs of the VPT and compare those to the benefits of the intervention and understand whether the VPT represents value for money from an NHS perspective. If an effect is observed, then models will estimate the health impacts, costs, and potential savings over a longer time period (eg, 10 years) and for a national rollout.

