##### Methods

A within-study analysis will determine the short-term cost-effectiveness of offering VPT relative to not offering VPT within EDs. Estimates derived from this study will be used to inform a long-term decision analytic model examining the cost-effectiveness of providing, versus not providing, VPT within EDs over a longer time horizon. Alternative perspectives for the analysis will be considered, with the NHS perspective being the base case. Cost-effectiveness will be presented using standard statistics.

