##### Long-Term Cost-Effectiveness Analysis

A Markov decision model with quarterly cycles will be used to estimate the cost-effectiveness of offering VPTs in EDs. To determine cost-effectiveness using a health and social care perspective (primary analysis), the Markov model will be health-state based, with key health states likely to be healthy, injured, or dead. To support a multisector perspective (secondary analysis), the Markov model will be event-based.

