##### Time Horizon

The time horizon for the decision analytic model will extend beyond the time frame of this study to encompass a period of time where, if possible, all relevant costs and outcomes for this appraisal have been accrued [63].

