## Discussion

### Principal Findings

We hypothesize that, for Objective 1, we will find a reduction in ED attendance. Objective 2 is exploratory and arose through PPIE; while we expect that some patients may not be willing to disclose their exposure to violence, the extent of this effect in ED is not known. We hypothesize that the intervention will be cost-effective over a 10-year time horizon and from the perspective of the NHS.

As far as we are aware, this project will not only provide the first robust evaluation of violence prevention activities in ED, but the data available will also provide an unprecedented opportunity to consider some of the pathways that patients follow before, during, and after their attendance in ED. Ongoing PPIE and stakeholder engagement have already shaped the study objectives and methods. However, we are particularly interested in exploring some of the characteristics of patients that expose them to violence. There is growing interest in neurodevelopment conditions [70], and it is feasible that secondary analyses could inform the future design of ED-based violence prevention initiatives. Furthermore, there is a paucity of information on the costs and health consequences of violence. The primary outcomes from this effectiveness and cost-effectiveness evaluation will offer novel insights to the benefit of future research and therefore violence prevention. We anticipate future research might therefore focus on how intersectional vulnerabilities, such as neurodevelopmental conditions, age, gender and ethnicity, and how they interact with residential deprivation to influence the likelihood of serious violence.

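### The objectives run the long-term economic model only if an undefined effect is observed, while the methods plan it unconditionally and the 10-year hypothesis depends on it

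*Protocol article*

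**What the plan says.** The abstract (Objective) states: "If an effect is observed, then models will estimate the health impacts, costs and potential savings over a longer time (eg, 10 years) period". Aims and Objectives repeats the condition for Objective 3 in nearly the same words: "If an effect is observed, then models will estimate the health impacts, costs, and potential savings over a longer time period (eg, 10 years"), and the same sentence goes on to a national roll-out. Neither place says which outcome, estimate or threshold counts as an effect.

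The economic methods contain no condition:

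- Objective 3, Methods: "Estimates derived from this study will be used to inform a long-term decision analytic model". The same paragraph plans a within-study analysis, also unconditional, for short-term cost-effectiveness.
- Long-Term Cost-Effectiveness Analysis: "A Markov decision model with quarterly cycles will be used to estimate the cost-effectiveness of offering VPTs in EDs". The health-state version of this model is labelled the primary analysis.
- Time Horizon: "The time horizon for the decision analytic model will extend beyond the time frame of this study".

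Principal Findings then gives the hypothesis: "We hypothesize that the intervention will be cost-effective over a 10-year time horizon and from the perspective of the NHS".

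**The concern.** Whether the primary economic model is run is a protocol-level decision, and the article gives two answers. A cost-effectiveness result depends on expected costs and benefits and on their uncertainty, so an effect estimate that is null or imprecise still yields a result. A programme with a real cost and little measurable benefit is probably not good value, and a wide interval means the decision is uncertain. Commissioners need both of those answers. A condition on the observed effect removes them from the long-term analysis.

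There is a second consequence. If only estimates that pass a filter reach the model, those estimates are on average too favourable, and the planned probabilistic sensitivity analysis would be centred on the filtered value. How much this matters has to be calculated.

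**Working it through.** **1. The passages side by side**

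| Place in the article | Is the long-term model conditional? |
|---|---|
| Abstract, Objective | Yes, on an observed effect |
| Aims and Objectives, Objective 3 | Yes, on an observed effect |
| Objective 3, Methods | No |
| Long-Term Cost-Effectiveness Analysis | No; contains the primary analysis |
| Time Horizon | No; extends past the study |
| Principal Findings | Hypothesis stated at 10 years |

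The within-study analysis is limited to the short term (outcomes followed for 12-48 months), so it cannot answer a 10-year hypothesis. If the condition fails, nothing else in the plan does.

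**2. The plan's own design figure**

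Sampling gives α=.05, β=.90, a hazard ratio (HR) of 0.8 and 845. Reading .90 as power and the test as two-sided, Schoenfeld's formula with equal groups gives

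events = 4(1.960 + 1.282)² / (ln 0.8)² = 4 × 10.51 / 0.0498 ≈ 845.

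The figure reproduces as a number of events, and I use it as such.

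**3. Selection of the effect input**

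Assumptions: 'observed' means two-sided p<.05 in favour of the intervention, and the estimated log HR is normal with SE = 2/√events. With m = ln HR and a = (−1.96·SE − m)/SE:

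- probability that the model runs = Φ(a)
- mean log HR entering the model = m − SE·φ(a)/Φ(a)
- exaggeration = that mean divided by m.

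At HR 0.8 and 845 events: SE = 2/√845 = 0.0688; a = (−0.1349 + 0.2231)/0.0688 = 1.28; Φ(a) = 0.90. The mean is about −0.2365, so the exaggeration is 0.2365/0.2231 = 1.06.

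Projected sample: 2,500 + 900 = 3,400 engaged patients (Sampling), matched 1:1 (the minimum under Matching). I take 23% one-year reattendance as the control rate; the article reports it for patients who did not engage. First events only. At HR 0.8 the treated proportion is 1 − 0.77^0.8 = 0.189, so events = 3,400 × (0.23 + 0.189) ≈ 1,424.

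| True HR | Events | P(model runs) | Mean HR entering | Exaggeration of log HR |
|---|---|---|---|---|
| 0.80 | 845 | 0.900 | 0.789 | 1.06 |
| 0.80 | 1,424 | 0.988 | 0.799 | 1.01 |
| 0.85 | 845 | 0.656 | 0.818 | 1.24 |
| 0.85 | 1,459 | 0.874 | 0.840 | 1.08 |
| 0.90 | 845 | 0.334 | 0.835 | 1.71 |
| 0.90 | 1,495 | 0.531 | 0.866 | 1.37 |
| 0.95 | 845 | 0.112 | 0.845 | 3.28 |
| 0.95 | 1,530 | 0.169 | 0.880 | 2.49 |

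Under a weaker condition, a point estimate below 1, the projected sample gives 1.00 at HR 0.80, 1.03 at 0.90 and 1.29 at 0.95.

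Without any condition the model always runs and its input is not selected.

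**The case against.** The milder reading is that the conditional sentence is a summary which couples the longer horizon with a national roll-out. Making a roll-out projection depend on an effect is sensible, and the detailed methods, which are unconditional, would ordinarily govern. That is a fair account of what may have been meant, and it supports the narrower fix below. It does not remove the conflict, because the sentence as written covers the 10-year estimates of health impacts and costs as well as the roll-out.

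Three stronger readings are tempting, and the article does not support them.

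- A reader might infer that the 10-year result will be seriously biased towards cost-effectiveness. No significance threshold is stated, and true effects weaker than HR 0.8 are not the article's design values. At the design effect the bias is about 1% to 6%. The primary analysis counts recurrent events and more controls are expected, both of which should add information.
- A reader might infer that a null result would leave Objective 3 with no economic answer. The within-study analysis is unconditional and would still give a short-term one. Only the long-term primary analysis and the 10-year hypothesis would be lost.
- A reader might infer that the horizon is left open to be chosen afterwards. Ten years is compatible with a horizon meant to "encompass a period of time where, if possible, all relevant costs and outcomes for this appraisal have been accrued", and its exact length can be fixed in the full protocol, which is not shown.

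It is also fair to say that the effect most naturally meant is that of Objective 1, since the Objective 3 overview builds quality-adjusted life years on reattendance and injury. The threshold remains undefined.

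**Conclusion.** The contradiction stands on the text alone and needs no assumption. Two places make the long-term model conditional on an undefined effect, three plan it unconditionally, and the primary economic analysis and the 10-year hypothesis both depend on it. If the condition were applied and failed, that analysis and hypothesis would be left unanswered.

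The selection effect is real in direction and small at the design HR of 0.8: about 6% on the log HR with 845 events and about 1% with the projected sample. It becomes material only if the true effect is weaker than planned, for example 37% to 71% at HR 0.90. These figures rest on the p<.05 reading, the assumed event counts and a simple Cox-type variance. The hazard ratio is also only a proxy for the model's inputs, which include panel-regression, cost and literature-based quality-of-life estimates.

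**What to change.** In the abstract and in Aims and Objectives, remove the condition from the long-term model, or confine it explicitly to the national roll-out projection. Run and report the long-term NHS analysis whatever Objective 1 shows, and carry the full uncertainty of the effect estimate into the probabilistic sensitivity analysis already planned under Sensitivity Analysis.

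The Results section says the Objective 1 analyses were completed in August 2025 and the Objective 3 analyses in January 2026, with the latter expected to be available in August 2026. A wording change can therefore no longer steer the analysis. The report should state whether the condition was applied and, if so, which effect and threshold were used. If the long-term analysis was withheld on that ground, it should be run and reported.

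The cost is small, because the model is already planned. The downside for the sponsor is that an unfavourable or uncertain incremental cost-effectiveness ratio must be reported if the effect is null.

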## Methods

### Intervention

A process and implementation evaluation that describes both the planned and implemented VPT intervention is available elsewhere [37] and is further described in a Template for Intervention Description and Replication (TIDieR; Multimedia Appendix 1 [38]).

